##### Maternal and neonatal process outcomes

Length of time from membrane sweep to the birth of a babyLength of time from formal induction of labour to the birth of a babyOverall length of maternal hospital stayLength of infant stay in NICU or equivalent

Baseline data to include age, obstetric history, parity and Bishop Score will be collected for all participants on the first vaginal exam at the time of randomisation.

#### Statistical methods and analysis

##### Sample size for pilot trial

As this is a pilot trial and not designed to evaluate the clinical effectiveness, we will not undertake a formal power analysis for sample size. We will seek to recruit 66 women per clinical site (132 women in total) over a 6-month period beginning in July 2020. This target represents 10% of that required for the definitive trial (see below) and is greater than that recommended as the minimum sample sizes for pilot studies [33]. Data obtained from this study will inform the power analysis for a definitive trial.

##### Sample size for definitive trial

The primary outcome for the definite trial will be the spontaneous onset of labour. National data demonstrate a spontaneous onset of labour rate of 54% in women without routine membrane sweeping to prevent post-term pregnancy. A sample size of 910 in the intervention arm and 455 in the control group (2:1 randomisation, 1365 total) will have sufficient power (at > 80%) to detect a 15% relative increase in the primary outcome measure, that is from 54% without membrane sweeping to 62% with membrane sweeping. These calculations assume alpha of 0.05 and the test is 2-tailed.

#### Criteria for progressing to the main definitive trial

The criteria for progressing to a future definitive trial are based on the primary feasibility objectives of the pilot trial. The pilot will be deemed suitable to continue to definitive trial when the following are achieved:
Recruitment
At least 30% of eligible women agree to participate in the trial and 130 women are randomised.Completeness of outcome data
Complete clinical outcome data that would be collected in the main trial collected from at least 90% of pilot trial participants.Clinician willingness to participate
At least 70% of participating clinicians within the two pilot sites agree that they would be happy to implement the MILO Study. Clinician’s views, experiences and acceptability of the MILO Study will be explored within focus group interviews.

Given the primary objective of the MILO Study is to assess the feasibility of conducting a definitive randomised controlled trial, we will evaluate recruitment and retention, adherence to the MILO protocol and reasons for non-compliance, and clinicians and women’s views, experiences and acceptability of the MILO Study. In the event the MILO Study does not meet the above criteria, these results will inform whether and how the design of the definitive trial as originally envisaged should be delivered or adapted.

#### End of trial discontinuation criteria

##### Individual participant

Withdrawal of informed consentDevelopment of exclusion criteria or other safety reasons during the studyIncorrect enrolment or randomisation of the participant (data retained for purpose of analysis)Unanticipated adverse event (consideration given to whether the participant should be discontinued)

##### Recruitment centre

Not reaching pre-specified recruitment targets (at least 30% of eligible women agree to participate in the trial and 130 women are randomised)Systemic non-adherence to protocol

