#### Setting

The MILO Study will be set in the antenatal outpatient departments in two Irish maternity hospitals.

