##### Trial

If IDMC requires termination of the study, e.g. futility analyses show no benefit to ongoing recruitment.

For the woman, the pilot trial is considered ended on discharge from the maternity hospital. For the infant, the pilot trial is considered ended on discharge from the maternity hospital or from the neonatal unit.

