##### Data analysis

All data will be analysed and reported in accordance with the 2010 CONSORT Extension Statement for the reporting of Pilot and Feasibility studies [34]. As this is a feasibility study with a relatively small sample size, formal hypothesis testing is not appropriate; rather, the purpose of any analyses will be to generate estimates to inform the planning of the definitive future trial. Suitable descriptive statistics and graphical summaries will be used to summarise participant characteristics. Means and standard deviations will be used for continuous variables and counts and percentages for categorical variables. Estimates of variation in main effects will be used to inform future sample size calculations. Estimates (with measures of uncertainty) of any interaction effect between the main effects of the embedded factorial design will also be undertaken. These will refine the design characteristics of the future definitive trial.

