## Trial status

The MILO Study will begin recruiting in February 2021.

It is anticipated that recruitment will be completed in September 2021.

Protocol version: 05 January 2021, version 1.2

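### The rule for discontinuing a recruitment centre uses the whole-pilot threshold of 130 randomised women, although each centre's own target is 66

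*Protocol article*

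**What the plan says.** All references are to the protocol article.

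- **Setting**: "The MILO Study will be set in the antenatal outpatient departments in two Irish maternity hospitals".
- **Sample size for pilot trial**: "We will seek to recruit 66 women per clinical site (132 women in total) over a 6-month period beginning in July 2020".
- **Criteria for progressing to the main definitive trial**, recruitment item, which applies to the pilot as a whole: "At least 30% of eligible women agree to participate in the trial and 130 women are randomised".
- **End of trial discontinuation criteria, Recruitment centre**: "Not reaching pre-specified recruitment targets (at least 30% of eligible women agree to participate in the trial and 130 women are randomised". Systemic non-adherence to the protocol is the other ground listed there.
- **End of trial discontinuation criteria, Trial**: "If IDMC requires termination of the study, e.g. futility analyses show no benefit to ongoing recruitment".
- **Data analysis**: "formal hypothesis testing is not appropriate; rather, the purpose of any analyses will be to generate estimates". The Primary outcomes section likewise excludes formal hypothesis tests, and the Clinical outcomes section says that these data are not collected to judge effectiveness.
- **Trial status**: recruitment is to start in February 2021, and "It is anticipated that recruitment will be completed in September 2021".

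**The concern.** The progression criterion and the centre rule use the same pair of numbers, but they answer different questions. The first asks whether the pilot as a whole recruited enough women to justify a definitive trial. The second asks whether one hospital should stop. The agreement percentage can move from one level to the other unchanged. The count cannot, and it was not rescaled.

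A rule that a fully successful centre meets has to be ignored or reinterpreted when it is applied, which removes the value of stating it in advance. If it were applied literally, a centre would be lost from a study whose primary objective is feasibility. With only two sites, each assigned one invitation timing in the study within a trial, closing one would also remove one of that study's two clusters.

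A smaller, related point concerns the trial-level rule that follows. It offers futility analyses as an example of why the monitoring committee might end the study, without saying futility of what.

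**Working it through.** **Inputs.** Two sites (Setting). 66 women per site and 132 in total (Sample size for pilot trial). 130 randomised as a pilot criterion (Criteria for progressing) and again as a centre criterion (Recruitment centre). 2:1 allocation (Randomisation and allocation concealment). 54% versus 62% spontaneous onset of labour, two-sided alpha 0.05 (Sample size for definitive trial).

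**1. The plan's own figure.** 2 × 66 = 132, as stated. The progression threshold of 130 is 130/132 = 98.5% of that total, so it fits the pilot as a whole.

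**2. Centre rule read per centre.**
- Threshold against target: 130/66 = 1.97, about twice the site target.
- A centre that meets its target reaches 66/130 = 51% of the threshold.
- Both centres together would need 2 × 130 = 260 women, against 132 planned.
- If one centre did reach 130, only 132 − 130 = 2 women would be left for the other. Within the planned total at least one centre must fail, and with the planned 66/66 split both do.

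**3. Centre rule read as the pilot total.** Both centres then meet or miss the count together. Two illustrations:
- 66 + 63 = 129 is below 130, so the centre that met its target is caught by the other's shortfall.
- 100 + 30 = 130 passes, so a centre at less than half its target is not flagged.

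On this reading the rule only repeats the progression criterion and contains no centre-level number.

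**4. Why simply halving the threshold is not enough.** A hard minimum of 130/2 = 65 per centre would fail the smaller centre in a 70/62 split. That split totals 132 and meets the pilot criterion, and the smaller centre is at 62/66 = 94% of its target. A 66/64 split, total 130, would also fail one centre.

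**5. Information in the pilot for futility on the clinical outcome.** With 132 women at 2:1 there are 88 and 44.
- Pooled proportion: (88 × 0.62 + 44 × 0.54)/132 = 0.593.
- Standard error under no difference: √[0.593 × 0.407 × (1/44 + 1/88)] = 0.0907.
- Standard error under the assumed rates: √(0.54 × 0.46/44 + 0.62 × 0.38/88) = 0.0912.
- Power: Φ[(0.08 − 1.96 × 0.0907)/0.0912] = Φ(−1.07) = 0.142, about 14%.
- 95% confidence interval half-width: 1.96 × 0.0912 = 0.179, about 18 percentage points against an assumed effect of 8.

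As a check, the same method at the definitive size of 455 and 910 gives 80.8%, in line with the stated power above 80%.

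**The case against.** The strongest defence is that the centre rule speaks of pre-specified targets and nearly repeats the progression wording, so it may be a cross-reference to the pilot total. A pilot of 132 then meets it, and no centre is closed in error. This is a fair reading, and it means that wrongful closure of both centres is not certain. It does not rescue the rule, because it leaves a centre rule without a centre figure (step 3).

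A reader might infer that all the discontinuation rules are unworkable. The text does not support that. The participant-level criteria and the non-adherence ground for a centre are untouched.

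A reader might also infer that the committee will run an efficacy futility analysis that the pilot forbids. The article does not say this either. Futility is given only as an example, the sentence refers to continuing recruitment, and the committee's stated task is to assess trial progress. Futility analyses are nowhere excluded by name; what is excluded is formal hypothesis testing and evaluation of effectiveness. A boundary or timing could properly sit in a committee charter or analysis plan. The article gives no look time or cut-off, so no probability of a futility stop can be calculated. What stands is that the word is ambiguous, and that one of its meanings would conflict with other sections.

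Finally, the two recruitment periods might look like a contradiction. The Discussion reports a pause caused by the pandemic, and Trial status gives the current dates. July 2020 is a stale date that the article itself explains.

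**Conclusion.** The centre-level recruitment rule is wrong as written. It takes the whole-pilot count of 130 and applies it under a centre heading, where the target is 66. Read per centre, it is triggered at both centres in a pilot that fully succeeds. Read as a total, it does not work as a centre rule. This follows from the article's own figures and needs no outside assumption.

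The consequence is limited to how the stopping rules operate; no estimate or analysis changes. It should be fixed, but it does not threaten the validity of the pilot.

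The futility wording is secondary and needs clarifying only. The 14% power figure rests on the definitive trial's assumed rates and on full recruitment at 88 versus 44. It shows why a stop based on the clinical outcome would have little information behind it, not that such a stop is planned.

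**What to change.** 1. **Trial level.** Keep 130 randomised women as a criterion for the pilot as a whole, and only there.
2. **Centre level.** Restate the rule on that centre's own figures: the proportion of its eligible women who agree, and its randomised women against its target of 66. State a tolerance for the count, and say that a centre is not failed on the count when the two centres together reach 130.
3. **Window.** Tie the centre rule to the current recruitment period in Trial status, and replace the July 2020 start date in Sample size for pilot trial.
4. **Futility.** In the trial-level rule, say that futility means recruitment or feasibility futility, so that it agrees with Primary outcomes, Clinical outcomes and Data analysis.

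The cost is a few sentences of protocol wording. Sample size, intervention and data collection do not change. The article says that recruitment has not yet begun, so the correction can be made before any centre is judged against the rule.

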##### Trial

If IDMC requires termination of the study, e.g. futility analyses show no benefit to ongoing recruitment.

For the woman, the pilot trial is considered ended on discharge from the maternity hospital. For the infant, the pilot trial is considered ended on discharge from the maternity hospital or from the neonatal unit.

#### Co-enrolment

Women enrolled in this trial may not take part in other interventional trials during the antenatal or intrapartum period evaluating induction of labour or cervical ripening.

#### Data collection, management and analysis

A data management plan will be completed outlining the data management process prior to the collection and analysis of study data.

##### Data collection forms

Paper forms will be used in each participating site to confirm eligibility prior to randomisation and to record informed consent. Data will be collected from the participating maternity hospitals using paper-based case report forms (CRFs). Data will be collected retrospectively by the research midwife in each site. The participating sites will collect the woman’s hospital number, and this may be used in the process of collecting missing data. With the exception of the on-site research midwife, the research team will only have access to a unique identifier for the participant for the purpose of data management. Clinical outcomes are recorded in a woman’s health care records, i.e. gestation, number of sweeps performed and gestation of woman at the time of membrane sweep, hyperstimulation, mode of delivery, analgesia, Apgar scores, length of stay and infant admission to NICU. This retrospective data from the clinical notes and the CRF are considered source data.

##### Storage of data

All identifiable information will be held on a secure, password-protected database accessible only to pre-defined personnel. Paper forms with identifiable information will be held in secure, locked filing cabinets. Personal data collected during the trial will be handled and stored in compliance with the 2018 General Data Protection Regulation (GDPR). Participants will be identified by a given code only. Data from the randomisation paper form, CRF and outcome data collected from women’s notes will be entered onto a purposefully designed Excel database, within 7 days of the woman’s discharge, by the research midwives. All entries to the database will be recorded and dated and each version archived to ensure good clinical practice. Entered data will later be double-checked against original forms for accuracy. All paper forms and data checking records will be securely archived after completion of trial as per requirements under the General Data Protection Regulation EU 2016/679. Direct access to the source data/documents will be required for trial-related monitoring by authorised personnel only.

##### Data analysis

All data will be analysed and reported in accordance with the 2010 CONSORT Extension Statement for the reporting of Pilot and Feasibility studies [34]. As this is a feasibility study with a relatively small sample size, formal hypothesis testing is not appropriate; rather, the purpose of any analyses will be to generate estimates to inform the planning of the definitive future trial. Suitable descriptive statistics and graphical summaries will be used to summarise participant characteristics. Means and standard deviations will be used for continuous variables and counts and percentages for categorical variables. Estimates of variation in main effects will be used to inform future sample size calculations. Estimates (with measures of uncertainty) of any interaction effect between the main effects of the embedded factorial design will also be undertaken. These will refine the design characteristics of the future definitive trial.

#### Reporting serious adverse events

Membrane sweeping has been found to be a low-risk intervention with no increased risk of infection or premature rupture of membranes. All adverse events will be reported to the trial team and recorded on the woman’s CRF. In addition, adverse events will be documented in the participant’s health records. An expected adverse event is discomfort during the membrane sweeping procedure.

### Work package 2: Health economic analysis

As this is a pilot trial, we will not undertake a formal economic evaluation. The health economic analysis will assess the feasibility of conducting a trial-based economic evaluation to examine the cost-effectiveness of membrane sweeping relative to expectant management and other methods of induction of labour to prevent post-term pregnancy. The basic tasks of economic evaluation are to identify, measure, value and compare the costs and outcomes of the alternative strategies being considered. The pilot study explores the feasibility of conducting an economic evaluation in this context and will seek to inform the design of the economic evaluation to be conducted alongside the definitive RCT. Evidence collected on resource use and outcome measures alongside the pilot RCT will provide the basis for the analysis. With respect to costing, a healthcare service perspective will be adopted, and the study will seek to identify the healthcare resource items that are relevant in this case. In particular, resource use associated with the implementation of the membrane sweeping intervention and the alternative expectant management and pharmacologic control strategies will be identified, measured and costed. In addition, other resource use over the course of the pregnancy in respect of antenatal, intrapartum and postnatal care will be identified, measured and costed. Unit costs will be identified and applied to convert data on resource use to resource costs, and total cost variables will be calculated. The pilot will involve the development and testing of appropriate data collection tools to undertake this process. For the pilot cost-effectiveness analysis, the alternative strategies will be compared on the basis of the clinical outcome data identified in the pilot RCT. This will inform costing models for the future definitive trial. For the cost-utility analysis, quality-adjusted life years (QALYs) will be modelled using the EuroQol EQ 5D-5L survey instrument. The pilot study will explore the feasibility, suitability and appropriate timing and delivery of the EQ 5D-5L in this context. To complete the pilot study, an incremental analysis will be conducted to model the mean costs and mean effect comparisons of the membrane sweeping intervention relative to the control strategies, which will inform the analysis models in the definitive trial. Univariate and multivariate sensitivity analyses, in addition to probabilistic methods through the estimation of cost-effectiveness acceptability curves, will be employed to explore uncertainty.

### Work package 3: Qualitative descriptive study

O’Cathain et al. [35] note the contribution qualitative research can make to feasibility studies by exploring uncertainties associated, for example, with interventions, trial methodology and outcome measures, prior to the conduct of a definite trial. Drawing on the guidance O’Cathain et al. [35] offer for such qualitative work, this feasibility study will include a qualitative descriptive study to explore the acceptability and feasibility of the MILO Study. This will include the clinician and women’s views of membrane sweeping, relevance and acceptance of the clinician training programme, and potential barriers and enablers to recruitment for a definitive trial.

#### Design

This work package will use a qualitative descriptive study design. Qualitative descriptive studies aim to explore and to understand the perspectives of those directly involved in certain processes or phenomenon [36], and so this design lends itself well to an exploration of the views of key stakeholders participating in the MILO Study.

#### Participants

Purposeful sampling will be used. Up to 10 women per clinical site (this target represents 15% of MILO participants) and all clinicians participating in the pilot trial will be invited to participate in the focus group interviews. All potential participants will be contacted via letter when the last trial participant has been discharged from the maternity unit and invited to participate in one of two focus groups based on their geographical location. All letters will make clear the number of participants required. The experiences and views of women across the control and intervention groups will be explored in order to provide an insight into all aspects of the feasibility study.

#### Data collection

Data will be collected via focus group interviews carried out in each participating site with two focus groups for each of clinicians and women stakeholders (four focus groups in total). The sessions will be led by an experienced qualitative researcher. A topic guide, informed by the purpose of the study and by the literature, will be used to guide the focus groups.

#### Data analysis

Focus groups will be audio-recorded, and recordings will be transcribed verbatim and entered into Nvivo. A pseudonym will be given for each participant and will be used on all transcripts of interviews. Data will be analysed using the framework method, a method of analysis for qualitative data described by [37]. Identified themes will inform the design of a future definitive trial.

### Work package 4: Study within a trial

#### Background

Adequate recruitment of trial participants is essential to the success of all trials. Yet, two thirds of trials will not complete recruitment within their stated time frame [38]. Pregnant women in particular remain underrepresented in clinical research, and the recruitment of pregnant women to trials has proved challenging [39]. A 2018 Cochrane systematic review examining the methods to improve recruitment to randomised controlled trials found a distinct knowledge gap in evidence-based recruitment strategies [40]. A study within a trial (SWAT) provides an opportunity to increase the evidence base about trial processes (e.g. recruitment and retention).

#### Aim

To evaluate the effect of the timing of the invitation to women to take part in the trial on recruitment and retention.

